**Treatment Plan**:

- Sutent be administered PO QD from days 1 to 28 (see Figure 1)

Figure 1. Treatment Schema

Determine eligibility

**↓**

| **REGISTER** | **Treatment** | Days  1-7 | 8-12 | 13-14 | 15-19 | 20-28 | 29-42 |
| --- | --- | --- | --- | --- | --- | --- | --- |
| XRT |  | X |  | X |  |  |
| Sutent | X | X | X | X | X |  |

**↓**

Additional chemotherapy (as determined by Medical Oncology)

**↓**

Maintenance Sutent (until death or progression) and appropriate follow-up

- Radiation therapy will start on day 8 and will be given to each site for ten fractions
- Fractions must be separated by at least 16 hours
- The MTD of radiation in combination with Sutent will be determined
- Doses of radiation and Sutent will increase as shown in Table 1 in order to determine the MTD of radiation in Gy and Sutent in mg
- The RPTD will be one dose level lower than the MTD. If the MTD is not reached at dose level 5, no further escalation will occur and this will be the RPTD. The RPTD will then be used for future phase II trials.
- Starting day 43, chemotherapy may be given, as determined by the treating medical oncologist.
- Two weeks after completion of any chemotherapy, maintenance Sutent in 6 week cycles (consisting of Sutent 50 mg PO QD weeks 1-4 followed by no treatment weeks 5-6) until progression or death
- If no chemotherapy is planned, maintenance Sutent (as described above) will start on day 43.

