11. Radiation is to be delivered to each site over 10 fractions separated by at least 16 hours. Up to 5 sites may be treated. **(Added 7/27/06)** For patients with 3 to 5 sites of disease, it may be difficult to treat all sites of disease during one day. For these patients, an acceptable variant is to treat all 2 to 3 sites during days 8 to 19 and to treat the remaining sites on days 20 to 33. For these patients only, concurrent Sutent will continue until day 42.
12. Radiation Doses (Phase I): A phase I escalation of doses will be performed in order to determine in MTD in Gy

Doses of radiation will increase as follows in order to determine the MTD of radiation in combination with Sutent:

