**Table 1. Phase I Dose Levels**

| **Dose Level** | **Radiation Dose** | **Sutent Dose** |
| --- | --- | --- |
| 1 | 40 Gy in 10 fractions | 25 mg PO QD |
| 2 | 40 Gy in 10 fractions | 37.5 mg PO QD |
| 3 | 50 Gy in 10 fractions | 37.5 mg PO QD |
| 4 | 50 Gy in 10 fractions | 50 mg PO QD |
| 5 | 60 Gy in 10 fractions | 50 mg PO QD |

.

Phase I dose escalation will proceed according to a “3+3” design. After 3 patients have been treated on each dose level, they will be followed for at least 30 days. If 0 of 3 patients have DLTs, the dose will be escalated to the next dose level. If ≥2 of 3 patients have DLTs, dose escalation will be terminated and the next lowest dose level will be declared the maximal tolerated dose for Phase II evaluation. If 1 of 3 patients has a DLT, then three more patients will be treated at the same dose level and if the incidence of DLT among six patients is < 2 of 6, the dose will be escalated to the next level for that site.

- Grades 3-5 non-hematological toxicities (excluding nausea, vomiting, and alopecia) and Grade 4-5 hematological toxicities will be referred to as dose limiting toxicities (DLT).
  - Esophagitis and mucositis are very common side effects with radiation therapy and grade 3 side effects can be seen after palliative courses of radiotherapy. Therefore, grade 3 mucositis or esophagitis lasting ≤ 7 days will **not** be considered a DLT. If the grade 3 mucositis or esophagitis lasts > 7 days, it will then be considered a DLT.
- The recommended phase II dose will be 1 dose level below the defined MTD or at the maximum tested dose if the MTD has not been reached.

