**11. ADDITIONAL INTERVENTIONS – CHEMOTHERAPY, SURGERY AND/OR ADDITIONAL RADIATION**

11.1 Interventions prior to protocol therapy: If chemotherapy, surgery and/or radiation are recommended by the treating physicians based on the patient’s clinical needs, they may be performed two weeks before or after days 1-28 of protocol therapy.

For instance, a patient with a history of breast cancer status post mastectomy (three years ago) and adjuvant chemotherapy now presents with a solitary brain metastasis, a single lung lesion and two bone lesions. The brain metastasis and lung lesion are both amenable to resection. Subsequently, the patient receives whole brain radiation and taxane based chemotherapy. After chemotherapy, CT of the chest abdomen and pelvis and MRI of the brain reveal no evidence of metastatic disease but bone scan demonstrates residual uptake in the two bone lesions. Two weeks after completion of chemotherapy, the patient is eligible for protocol therapy. The patient will receive Sutent on days 1-28 and extracranial stereotactic radiation on days 8-12 and 15-19 as per protocol. Two weeks after protocol therapy (day 43), the patient may receive additional chemotherapy. After completion of all planned chemotherapy, the patient will start maintenance Sutent. Therefore, all of the chemotherapy, surgery and whole brain radiation are allowed by protocol but are not considered “on protocol therapy”. While all toxicities of these interventions will be documented and recorded, any toxicity resulting from non-protocol therapy will not count as dose-limiting toxicity.

11.2 If patients have documented progression during additional chemotherapy and/or maintenance Sutent, the patient will be taken off protocol. At that time, any necessary intervention (chemotherapy, surgery and/or radiation will be allowed).

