**16. STATISTICAL CONSIDERATIONS**

- Phase I: The primary objectives are to determine the maximum tolerated dose (MTD) and dose limiting toxicity (DLT) of extracranial stereotactic radiation therapy in combination with Sutent when given to all sites of involved disease in patients with metastatic cancer.
- For dose escalation purposes, the major endpoint will be dose-limiting toxicity occurring within 30 days after the start of radiation therapy.
- Dose limiting toxicity is defined as follows: Grade 3-5 non-hematological toxicities (excluding nausea, vomiting, and alopecia) and Grade 4-5 hematological toxicities.
  - Esophagitis and mucositis are very common side effects with radiation therapy and grade 3 side effects can be seen after palliative courses of radiotherapy. Therefore, grade 3 mucositis or esophagitis lasting ≤ 7 days will not be considered a DLT. If the grade 3 mucositis or esophagitis lasts > 7 days, it will then be considered a DLT.
- The MTD for a specific area will be exceeded if 2 or more patients out of 6 (or a third or more) with disease at that site experience DLT at that dose. The dose immediately below will be recommended for further study.
- Phase II: *(Includes 3 to 6 patients from Phase I MTD):* The median progression free survival with optimal chemotherapy alone for the 4 most common tumor types (lung, breast, prostate and colorectal) ranges from 2.2 to 10.6 months, depending on primary tumor site and degree of pretreatment. Therefore, we will assume a median time to progression of 6.4 months (standard deviation 3.2 months) with chemotherapy alone. With 38 patients, this study has 87% power (α=0.05) to detect a 25% increase in time to progression. Also the 2 year freedom from progression is <5% with chemotherapy therapy and this study has 70% power (α=0.05) to demonstrate a 10% absolute increase in 2 year progression-free survival.
  - All patients included in the study will be assessed for response to treatment, even if there are major protocol treatment deviations or if they are ineligible (intent-to-treat population). Criteria described in Section 10 will be used to assign each patient to one of the following response categories: 1) complete response, 2) partial response, 3) stable disease, 4) progressive disease, 5) early death from malignant disease, 6) early death from toxicity, 7) early death because of other cause, or 8) unknown (not assessable, insufficient data).

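### The two-batch radiation option (radiation to day 33, Sutent to day 42) was added without adapting the 30-day DLT window or the day-43 restart

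*Protocol*

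**What the plan says.** The standard course gives Sutent on days 1–28 and radiation on days 8–12 and 15–19 (Section 3 schema). Section 8.1, item 11, in text marked as added on 7/27/06, allows a variant for patients with three to five sites. Some sites are treated on days 8–19 and the rest on days 20–33. "For these patients only, concurrent Sutent will continue until day 42".

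The rules that depend on the length of the course read as follows:

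- **Escalation endpoint (Section 16):** "the major endpoint will be dose-limiting toxicity occurring within 30 days after the start of radiation therapy". Section 12 draws the line between acute and late toxicity at the same 30 days and grades later events on a different scale.
- **Cohort follow-up (Section 10):** "After 3 patients have been treated on each dose level, they will be followed for at least 30 days".
- **Restart (synopsis, Treatment Plan):** "If no chemotherapy is planned, maintenance Sutent (as described above) will start on day 43", and "Starting day 43, chemotherapy may be given, as determined by the treating medical oncologist".
- **Reason for day 43 (Section 11.1, worked example):** "Two weeks after protocol therapy (day 43), the patient may receive additional chemotherapy". The same section says of chemotherapy, surgery and other radiation that "they may be performed two weeks before or after days 1-28 of protocol therapy".

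None of these refers to item 11. The Sutent schedule in the synopsis, Section 3 and Sections 9.1, 9.2, 9.4 and 9.9 does not refer to it either.

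**The concern.** Item 11 moves the end of radiation by two weeks and the end of concurrent Sutent by two weeks. The DLT window is tied to the start of radiation and the restart to a fixed calendar day, so neither moves with it.

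Two things are at stake. In phase I, a DLT in the last days of a two-batch patient's concurrent treatment, or soon after the second batch, need not count when the next dose level is opened. In both phases, the two-week rest that the protocol builds in before further therapy disappears for the patients who have just had the longest concurrent course. At dose levels 1–3 the daily Sutent dose also rises to 50 mg with no break.

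**Working it through.** **Inputs.** Radiation starts on day 8 (synopsis, Treatment Plan). One batch: last fraction day 19, last concurrent Sutent dose day 28 (Section 3). Two batches: last fraction day 33, last concurrent dose day 42 (Section 8.1, item 11), taking the last fraction to fall on the last day of the stated interval. DLT window: 30 days from the start of radiation (Section 16). Maintenance: 50 mg daily, four weeks on and two off (Section 9.4).

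**1. The protocol's own day 43.** Last dose + 14 days off + 1 = 28 + 14 + 1 = 43. This reproduces, for the 28-day course only.

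**2. End of the DLT window.** 8 + 29 = day 37 if day 8 counts as the first day; 8 + 30 = day 38 if it does not.

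**3. What the window and day 43 give each schedule.**

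| | One batch | Two batches |
| --- | --- | --- |
| Window end minus last fraction | 37/38 − 19 = 18/19 days | 37/38 − 33 = 4/5 days |
| Window end minus last concurrent Sutent dose | 37/38 − 28 = +9/+10 days | 37/38 − 42 = −5/−4 days |
| Days off drug before day 43 | 43 − 28 − 1 = 14 | 43 − 42 − 1 = 0 |
| Longest unbroken Sutent run, no chemotherapy | 28 days | 42 + 28 = 70 days |

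At levels 1–3 the 70-day run steps up from 25 or 37.5 mg to 50 mg on day 43. At levels 4–5 the dose is already 50 mg.

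**4. Dates that would give two-batch patients the same terms.** Window: 33 + 18/19 = day 51/52 from the last fraction, and 42 + 9/10 = day 51/52 from the last Sutent dose, so both anchors agree. Restart: 42 + 14 + 1 = day 57. Extra DLT observation: from 42 − 38 = 4 days to 52 − 37 = 15 days.

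**5. Illustration of the effect on escalation.** The rates here are assumptions, not protocol figures. Under the Section 10 rule, P(escalate) = q³ + 3pq² · q³, where p is the per-patient probability of a DLT that counts and q = 1 − p. Take a cohort entirely on the two-batch schedule with a true DLT rate of 33%:

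| Share of DLTs outside the window | p | P(escalate) |
| --- | --- | --- |
| 0 | 0.33 | 0.434 |
| 25% | 0.2475 | 0.605 |
| 50% | 0.165 | 0.783 |

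With no two-batch patients in the cohort, the effect is nil.

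**The case against.** **On the window.** Section 10 holds the working escalation rules. It follows treated patients for at least 30 days before the counts are applied, and its DLT definition has no time limit. Section 16 names a major endpoint, not the only one. On that reading a day-40 event in a two-batch patient is seen and could count. This softens the point, and it would be too strong to say that such events are certainly lost. But Section 10 sets a length of follow-up and does not redefine the endpoint. Section 16 and the acute/late cut in Section 12 both still run from the start of radiation, and the synopsis escalation rule speaks of acute toxicity. At best the sections disagree for these patients. It is also fair that the window covers 37–38 of the 42 Sutent days. The larger loss is the time after the last fraction.

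**On day 43.** Section 11.1 can be read as a two-week rule, with day 43 only its result for an example patient with two bone lesions, who could not use the variant. Applied to item 11, that rule gives day 57. Chemotherapy from day 43 is optional. Both points are right, but the synopsis states day 43 outright for maintenance without chemotherapy, and Section 11.1 itself ties the two weeks to days 1–28. The 70-day run needs a two-batch patient, no chemotherapy and a literal day 43.

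**On detection.** Follow-up visits every two weeks for two months, biweekly review and SAE reporting to 28 days after Sutent stops all continue. A reader should not infer that toxicity would go unnoticed; the gap is in what formally counts.

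**Conclusion.** The point holds for two rules. Read literally, the escalation endpoint closes 4–5 days before a two-batch patient's last concurrent Sutent dose and leaves only 4–5 days after the last fraction. The day-43 start removes the 14-day break and allows 70 consecutive Sutent days. The day counts follow from the protocol's own dates. How much they matter depends on how many patients use the option, which the protocol does not state: from none to a whole cohort.

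Three stronger inferences are not supported:

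- **That Section 9 contradicts item 11 on how long Sutent is given.** Item 11 is a specific exception and governs; the unqualified days 1–28 elsewhere lacks only a cross-reference.
- **That pooling 28-day and 42-day courses in one DLT count is an error, or calls for a schedule-specific MTD.** Dose levels are defined by Gy and daily mg, which the variant leaves unchanged. No stated rule is wrong, and tabulation by schedule can be left to the SAP.
- **That blaming later toxicity on chemotherapy hides DLTs.** Section 11.1 does say that "any toxicity resulting from non-protocol therapy will not count as dose-limiting toxicity". Under Section 16, though, the window has closed before day 43 on either schedule, so attribution after that day changes nothing.

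**What to change.** For patients treated under Section 8.1, item 11:

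- **DLT window.** Extend the Section 16 window, and the acute/late cut in Section 12, to at least day 42. About day 52 is preferable, because it keeps the 9–10 days after the last Sutent dose that one-batch patients get. State that the Section 10 escalation decision is taken after that window.
- **Restart.** In the synopsis and Section 11.1, replace the fixed day 43 (and the reference to days 1–28) with two weeks after the last concurrent Sutent dose. This remains day 43 for one batch and becomes day 57 for two. Make both changes together: a window to day 52 with a restart on day 43 would overlap the new treatment.
- **Cross-references.** Refer to item 11 in Sections 3, 9, 10, 11, 12 and 16.

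The cost is protocol wording. Two-batch patients need 4–15 more days of DLT observation, which can delay an escalation decision by as much, and they start maintenance or chemotherapy 14 days later. One-batch patients are unaffected and no patients are added.

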**Phase I Dose Levels**

| **Dose Level** | **Radiation Dose** | **Sutent Dose** |
| --- | --- | --- |
| 1 | 40 Gy in 10 fractions | 25 mg PO QD |
| 2 | 40 Gy in 10 fractions | 37.5 mg PO QD |
| 3 | 50 Gy in 10 fractions | 37.5 mg PO QD |
| 4 | 50 Gy in 10 fractions | 50 mg PO QD |
| 5 | 60 Gy in 10 fractions | 50 mg PO QD |

1. Radiation Doses (Phase II): The radiation dose used in the MTD dose level will be used throughout the phase II portion of this study.
2. Dose/volume constraints: The dose distribution will be converted to the normalized isoeffective dose, equivalent to dose given at standard fractionation (2 Gy per fraction). Normal tissue tolerance doses to be used as guidelines for treatment plan evaluation are: (based on the treatment on the sum of all involved sites):
3. Spinal cord:
   - 1. Must keep each dose < 300 cGy/fraction (therefore maximum total spinal cord dose will be 3000 cGy)
     2. Same segment of spinal cord must not be in more than 1 treatment field
   1. Skin: Maximum skin dose 40 Gy
   2. Lung: Volume receiving > 20 Gy less than 30%
   3. Liver: Volume receiving > 30 Gy less than 50%
   4. Kidney: Volume receiving > 20 Gy (both kidneys) should be less than 50%
   5. Esophagus: Maximum esophageal dose ≤ 40 Gy
   6. Heart: Volume >25 Gy less than 60% and maximum heart dose <30 Gy
   7. Major Vessels: Maximum dose 40 Gy
   8. Bone marrow: Must limit the radiation to < 30% of bone marrow

**9. DRUG THERAPY - SUTENT**

9.1 Phase I Dose (days 1-28):

| **Dose Level** | **Radiation Dose** | **Sutent Dose** |
| --- | --- | --- |
| 1 | 40 Gy in 10 fractions | 25 mg PO QD |
| 2 | 40 Gy in 10 fractions | 37.5 mg PO QD |
| 3 | 50 Gy in 10 fractions | 37.5 mg PO QD |
| 4 | 50 Gy in 10 fractions | 50 mg PO QD |
| 5 | 60 Gy in 10 fractions | 50 mg PO QD |

9.2 Phase II Dose (days 1-28): Phase II will be the MTD from Phase I

9.3 Phase I and II Maintenance dose: will be 50 mg PO QD

9.4 Schedule:

- One days 1-28, Sutent will be taken p.o. in the morning
- Two weeks after completion of any chemotherapy, maintenance Sutent in 6 week cycles (consisting of Sutent 50 mg PO QD weeks 1-4 followed by no treatment weeks 5-6) until progression or death

9.5 Formulation and Packaging: SU011248 is a small molecule inhibitor of the receptor tyrosine kinases VEGFR, PDGFR, KIT, and FLT3. In this clinical trial, study medication of SU011248 refers to the investigational agent SU011248 L-malate. Sunitinib L-malate salt will be supplied as hard gelatin capsules containing 12.5-mg, 25-mg, and 50-mg equivalents of Sunitinib malate free base, in bottles containing 30 capsules each."

9.6 Storage:Store at 25º C (*77º F*); excursions permitted to 15-30º C (*59-86º F*).

9.7 Adverse Effects: Data regarding the safety of Sutent are largely from a Phase III randomized trial of 304 patients with metastatic GI stromal tumors following imatinib failure who were treated with Sutent vs. placebo and 169 patients with metastatic renal cell carcinoma treated on phase II trails (32, 33).

Cardiac: Left Ventricular Dysfunction – The incidence of decreased left ventricular ejection fraction to below the lower limit of normal is 11-15% with Sutent vs. 3% for placebo. Over 40% of patients recover left ventricular ejection fraction without intervention. Only 1% of patients suffered grade 3 left ventricular systolic toxicity. Sutent should be discontinued in the presence of clinical congestive heart failure. The Sutent dose should be reduced in all patients without clinical congestive heart failure but with an ejection fraction of <50% and a drop of over 20% from baseline.

Hemorrhagic Events: Bleeding occurred in 18 to 26% of patients receiving Sutent vs. 17% for placebo with epistaxis being the most common hemorrhagic event. The incidence of Grade 3-4 bleeding is 1 to 7% among patients receiving Sutent vs. 9% for placebo. However, fatal pulmonary hemorrhage was noted in two patients with non-small cell lung cancer. Bleeding events, including fatal GI bleeding, has been noted in patients within 30 days of completing Sutent. Although there is no specific contraindication for concurrent anticoagulants, patients requiring continued Coumadin, lovenox, heparin, NSAIDs, aspirin, plavix or similar drugs will be excluded from this study (12/16/09).

Hypertension: Hypertension was noted in 15 to 28% of patients receiving Sutent vs. 11% for placebo. Grade 3 hypertension occurred in 4 to 6% of patients receiving Sutent vs. 0% for placebo. No case of grade 4 hypertension was reported. Careful monitoring and use of antihypertensive therapy is recommended. Sutent should be discontinued in cases of severe hypertension (defined as >200 mgHg systolic or >110 mgHg diastolic).

Adrenal: Adrenal toxicity was noted in rats and monkeys treated with Sutent but to date, there have been no cases of clinical adrenal insufficiency, adrenal necrosis or hemorrhage in human clinical trials. Nonetheless, patients receiving Sutent that experience stress such as surgery, trauma or severe infection should be monitored for adrenal insufficiency.

Gastrointestinal: Diarrhea, nausea, stomatitis, dyspepsia and vomiting were the most commonly reported gastrointestinal events occurring in patients who received Sutent. Diarrhea and stomatitis occurred more commonly in patients treated with Sutent than placebo. Supportive care for gastrointestinal adverse events, such as anti-nausea or anti-diarrheal medication should be prescribed as needed.

Skin: Skin discoloration, often to a yellowish hue occurred in approximately 1/3 of patients treated with Sutent. Depigmentation of the hair or skin, dryness, cracking, blistering or rash was also reported.

9.8 Potential Drug-Drug Interactions: SU11248 is mediated metabolized by the liver by CYP3A4. Therefore CYP3A4 inducers such as rifampin will result in a 56-79% reduction in SU11248 serum doses while CYP3A4 inhibitors such as ketoconazole will result in a 59-76% increase in SU11248 serum doses. For patients who are being concomitantly treated with a potent CYP3A4 inhibitor or CYP3A4 inducer, alternative treatments that lack potent CYP3A4-inducing properties should be considered. For patients who require treatment with a potent CYP3A4 inhibitor, a dose reduction should be considered in the presence of severe adverse events. For patients who require treatment with a potent CYP3A4 inducer, a dose increase should be considered.

However, in-vitro studies indicate that SU11248 does not induce or inhibit the major CYP450 enzymes including CYP3A4.

9.9 Administration: Sutent may be taken with or without food. The following schedule is recommended for the phase I and phase II studies:

| **REGISTER** | *Treatment* | *Days*  *1-7* | *8-12* | *13-14* | *15-19* | *20-28* | *29-42* |
| --- | --- | --- | --- | --- | --- | --- | --- |
| XRT |  | X |  | X |  |  |
| Sutent | X | X | X | X | X |  |

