9.10 Dose Modifications for Sutent(Applies only to phase II)

Dose modification of Sutent can be secondary to any grade 3 toxicity related to Sutent according to the judgment of the treating physician. When toxicities eliciting dose modification occur, Sutent will be temporarily discontinued but restarted at the next lower dose level when the toxicity has resolved to grade 2 or lower. In the event of hospitalization for reasons other than drug toxicity, patients should be directed to continue trial drug at the discretion of their physician. The principal investigator should be notified immediately of any compliance issues that arise in the course of the trial. If a patient still experiences dose-modifying toxicities despite drug holiday and reduced dose schedule, the patient, if benefiting from treatment, should stop receiving Sutent and continue radiation.

The following toxicities, in addition to any other toxicity as judged by the treating physician, merit temporary discontinuation should be considered dose-limiting toxicity:

1. Any CTC grade 3 or 4 non-hematopoietic adverse event that the investigator considers consistent with a drug-related toxicity;

2. Any CTC grade 4 hematopoietic adverse event that the investigator considers consistent with a drug-related toxicity;

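### Maintenance Sutent is fixed at 50 mg with no exception for earlier toxicity; the dose-modification rule in Section 9.10 is not reconciled with it and leaves phase I out

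*Protocol*

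**What the plan says.** Section 9.3 of the Protocol reads "9.3 Phase I and II Maintenance dose: will be 50 mg PO QD". Section 9.4 gives the schedule: "maintenance Sutent in 6 week cycles (consisting of Sutent 50 mg PO QD weeks 1-4 followed by no treatment weeks 5-6) until progression or death". The synopsis Treatment Plan, Section 3 and Section 9.9 repeat this. Maintenance begins two weeks after any chemotherapy ends. Otherwise, "If no chemotherapy is planned, maintenance Sutent (as described above) will start on day 43".

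The dose levels in Section 9.1 apply to days 1-28. Level 1 is "1 | 40 Gy in 10 fractions | 25 mg PO QD" and level 2 is "2 | 40 Gy in 10 fractions | 37.5 mg PO QD". Level 3 also uses 37.5 mg, and levels 4 and 5 use 50 mg.

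The only general rule for changing the Sutent dose is headed "9.10 Dose Modifications for Sutent(Applies only to phase II" (closing bracket omitted here). Under it, "Sutent will be temporarily discontinued but restarted at the next lower dose level when the toxicity has resolved to grade 2 or lower". If toxicity recurs at the reduced dose, Sutent stops and radiation continues.

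Other provisions are narrower. Section 6 lets the investigator discontinue a patient and lists adverse events among the reasons. Section 9.7 covers heart failure, ejection fraction and severe hypertension. Section 9.8 covers potent CYP3A4 inhibitors and inducers.

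**The concern.** The maintenance sentence covers both phases and has no exceptions; the reduction rule covers one phase and states no period. Where the two meet, the Protocol does not say which governs. The patients concerned are those who already have documented toxicity, so a literal reading can put them on a higher daily dose than the one at which the toxicity occurred, in cycles that run until progression or death.

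Two investigators could treat the same patient differently and both claim to follow the Protocol. Maintenance toxicity, and the exposure behind phase II progression-free survival, would then depend in part on how each of them resolved the gap.

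**Working it through.** There is no stated power or sample-size figure to reproduce here. The check compares the passages and does simple arithmetic on the dose table and the study calendar.

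**1. Size of the step to 50 mg (Section 9.1 against 9.3)**
- Level 1: 50 / 25 = 2.0. Over 28 dosing days, 28 × 25 = 700 mg against 28 × 50 = 1400 mg.
- Levels 2 and 3: 50 / 37.5 = 1.33. Over 28 dosing days, 28 × 37.5 = 1050 mg against 1400 mg.
- Levels 4 and 5: no step, unless the patient has been reduced.

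**2. Phase I patient with a DLT at 25 or 37.5 mg**
- 9.3 names phase I and gives 50 mg.
- 9.10 excludes phase I by its heading.
- Section 6 permits discontinuation but neither requires it after a DLT nor gives a modified dose.
- 9.7 and 9.8 apply only to particular events or co-medication.
- Result: unless the investigator stops treatment or one of those events applies, the 50 mg sentence is the only one that fits.

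**3. Phase II patient reduced under 9.10**
- If 9.10 covers the whole treatment, the lower dose would continue, but 9.3, 9.4 and 9.9 state 50 mg without reference to it.
- If 9.10 covers only the concurrent period, as its closing instruction to continue radiation suggests, 9.3 governs and the patient goes to 50 mg. Maintenance then has no general modification rule in either phase.
- Neither reading is stated. Phase I maintenance is uncovered under both.

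**4. How many phase I patients**
- Under the Section 10 rule, applied across the trial and not by site, a level that is passed has 0 DLTs in 3 patients or 1 in 6, so at most 1.
- A level that stops escalation has at least 2. The maximum is 3 in a single cohort of 3, or 1 + 3 = 4 if the second cohort is fully treated.
- Across levels 1 to 3 the count runs from 0 (no DLTs) to 1 + 1 + 4 = 6 (stopping at level 3).
- The number of phase II patients reduced under 9.10 cannot be derived from the Protocol.

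**5. Timing against the DLT window**
- Section 16 counts DLTs for escalation within 30 days after the start of radiation. Radiation starts on day 8, so the window closes at about 8 + 30 = day 38.
- The earliest maintenance day is 43, which is 43 − 38 = 5 days later.
- With chemotherapy the gap is longer: "Starting day 43, chemotherapy may be given, as determined by the treating medical oncologist".
- In the multi-site variant of Section 8.1, concurrent Sutent runs to day 42. Without chemotherapy, a day-43 start would follow with no break.

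**The case against.** The strongest reply is that the step-up is intended. Sections 9.1 and 9.2 confine the dose levels to days 1-28, 9.3 sets maintenance separately, and Section 2c cites 50 mg/day as the recommended dose from a phase I trial of Sutent in advanced cancers. Lower doses alongside radiation, then 50 mg afterwards, is a coherent plan. This stands for patients who tolerated their assigned level. A reader might infer that the step-up is itself a mistake, or that every phase II patient would be wrongly raised above the selected dose if a level from 1 to 3 is carried forward. The days 1-28 limit means the documents do not support either inference.

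Second, 9.3 can be read as the planned dose and 9.10 as its toxicity exception. No sentence says that a reduced patient returns to 50 mg. This also stands in part: for phase II the fault is an unresolved overlap, not a flat contradiction. It does not help phase I, which the heading of 9.10 excludes.

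Third, Section 6 allows discontinuation for adverse events in either phase, and a Section 10 DLT need not be due to Sutent; prolonged esophagitis counts, for example. So a DLT does not by itself show that the patient could not tolerate that Sutent dose, and a literal restart at 50 mg is not inevitable. But the choice is then between stopping altogether and 50 mg, left to discretion, with no stated rule between them.

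**Conclusion.** The point holds as a safety reconciliation for two groups: phase I patients with a DLT at 25 or 37.5 mg, and phase II patients reduced under 9.10. On a literal reading the first group goes to 2.0 or 1.33 times the dose at which the DLT occurred. For the second group the passages give no single answer. No general modification rule covers phase I maintenance. The planned step-up is a design choice, with the limitation that toxicity after it does not enter the escalation decision.

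The phase I group is small (0 to 6 patients under the Section 10 rule), and its importance lies in who those patients are. A reader might size the point by counting everyone at levels 1 to 3 (9 to 18 at 3 to 6 per level) and adding the 38 phase II patients. That sum is not supported: it counts patients for whom the step-up may be deliberate, and the groups can overlap because the 38 include 3 to 6 phase I patients.

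The timing statement rests on the Section 16 definition. Section 10 also asks for at least 30 days of follow-up per cohort without giving a clear starting point. Counted from day 28, that would reach day 58 (28 + 30) and overlap early maintenance, but Section 16 is the passage that defines the escalation endpoint.

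**What to change.** Reconcile Sections 9.3 and 9.4, and the repeats in the synopsis Treatment Plan, Section 3 and Section 9.9, with Sections 9.10 and 6 for patients with a prior DLT or dose reduction. Reconcile the phase II-only heading of 9.10 with the open-ended maintenance given to phase I patients, and state whether 9.10 extends beyond the concurrent period. The result should be one stated rule for each group. The sponsor chooses the rule and the dose. Nothing here requires maintenance to follow the assigned level.

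The cost is amendment wording, with no extra patients or procedures. The downside is that maintenance exposure may become slightly less uniform.
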